### Eligibility Criteria

Participants will be eligible for inclusion in the study if they meet the following criteria (Textbox 1):

Textbox 1.Participant inclusion and exclusion criteria.The following criteria were used to determine participant eligibility for the study.
**Inclusion criteria**
Age 18 years or olderDiagnosis of chronic musculoskeletal pain (CMP) by a licensed medical providerSelf-reported average pain intensity of ≥3 on a 0–10 numeric rating scale, experienced on most days over the past 3 monthsAbility to understand spoken and written EnglishAbility to complete online self-report questionnaires using a tablet or personal computer
**Exclusion criteria**
Inability to provide informed consent due to cognitive, psychiatric, or physical impairmentPrevious formal mindfulness training (eg, completion of Mindfulness-Based Stress Reduction or equivalent structured programs)Diagnosis of cancer at the time of enrollmentActive psychosis, suicidal ideation with intent or plan, or severe substance use disorder, as determined by a structured clinical interview (Mini-International Neuropsychiatric Interview [MINI])Presence of an unstable medical condition that could interfere with study participation or safetySurgery within the past 3 monthsReceipt of pain-relieving injections (eg, corticosteroid or hyaluronic acid) within the past 3 months

Relevant concomitant care is restricted during the trial. Patients are welcome to continue their usual medical care but are asked to refrain from beginning any new treatments during the study. Cortisone and hyaluronate injections are prohibited during the trial.

### Study Settings

All mindfulness training sessions and psychophysiological assessments will be conducted at the Complementary Health Innovation Lab (CHIL), located within Florida State University’s (FSU) College of Nursing. CHIL is equipped with a dedicated psychophysiology laboratory that integrates EEG and fNIRS systems, allowing for simultaneous data acquisition via a unified interface.

Sessions involving psychophysiological data collection (Sessions 1 and 4) will be conducted in a low-light environment to optimize the quality of fNIRS signal acquisition and more closely approximate real-world mindfulness settings. During these sessions, the participant, study therapist, and trained research assistant (RA) will be present. For Sessions 2 and 3, which do not involve psychophysiological data collection, only the participant and the therapist will be in the lab room. The treatment environment remains identical across all sessions, with the sole distinction being that the simultaneous EEG and fNIRS recording cap is worn only during the psychophysiology sessions.

Self-report measures will be administered during sessions, including assessments of self-transcendence and acute pain. All in-session measures will be completed using a tablet-based survey via the Qualtrics (Qualtrics International Inc) platform. Broader clinical assessments, including baseline and follow-up surveys at 1 week, 1 month, and 3 months, will be conducted remotely through Qualtrics at a time and location convenient for each participant.

### Assignment of Interventions and Blinding

Participants will be randomly assigned to intervention groups using a computer-generated randomization sequence created in Microsoft Excel. Randomization is stratified by opioid use (yes or no) to ensure balance across treatment arms on this clinically relevant variable. Within each stratum, participants are allocated using permuted block randomization with a fixed block size of 6 to maintain allocation concealment and prevent prediction of assignment. Treatment allocation is generated by personnel uninvolved in assessment or treatment and concealed on the private, password-protected computer of the uninvolved research member.

To preserve blinding, the randomization sequence will not be accessible to either assessment staff or the principal investigator (PI) until the study’s completion. Treatment allocation, for active treatment groups, will only be revealed to the interventionist immediately before the participant’s first treatment appointment. Outcome assessor blinding will further be ensured through the use of online, asynchronous self-report surveys, preventing any direct interaction between study personnel and participants.

Unblinding will only occur in exceptional circumstances where knowledge of the assigned intervention is essential for the clinical safety of the participant or to address a serious adverse event (AE). The request for unblinding must be made by the PI or a designated senior clinical investigator after determining that unblinding is necessary for participant safety or ethical oversight. The PI will document the rationale for unblinding and notify the institutional review board (IRB) if the event involves a serious adverse reaction or protocol deviation that may impact participant safety or data integrity.

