## Methods

### Overview

This will be a single-blind, randomized, 3-arm, parallel-group, clinical trial (2:2:1 allocation ratio). The planned flow diagram for this single-site RCT is presented in Figure 1. The protocol is reported according to the SPIRIT (Standard Protocol Items: Recommendations for Interventional Trials; Checklist 1) [41] checklist. This study was prospectively registered with the Open Science Framework on April 25, 2023.

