### Participants

We will recruit and enroll 173 adults with CMP who meet established eligibility criteria. Sample size estimation was conducted in 2 stages, reflecting an expansion from a sole focus on mechanistic sensitivity to the joint consideration of mechanistic and clinical relevance. The first stage was designed to detect changes in self-transcendence in order to elucidate an emerging therapeutic mechanism of MBIs, whereas the second stage broadened the scope of the study to contribute to a growing body of research evaluating the effects of brief MBIs on chronic pain.

First, our original power analysis using G*Power (Heinrich Heine University Düsseldorf) indicated that a total sample of 138 participants would provide sufficient power (*β*=.80) to detect changes in self-reported and psychophysiological indices of self-transcendence [42]. This target reflected a required analyzable sample of 110, inflated by 25% to account for expected attrition. To promote robust detection of mechanistic effects, we specified a conservative effect size ( Cohen *d*=0.30), representing half the smallest effect observed in our preliminary data (Cohen *d*=0.60). This approach was intended to support the more stringent comparison between the MB and MB+DP groups, while incorporating corrections for multiple comparisons.

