Second, to enhance the clinical interpretability of the intervention effects, we added a waitlist control group. This adjustment was made prior to participant enrollment. Inclusion of this no-treatment comparison group provides a benchmark against which to evaluate the specific impact of the MBIs on both mechanistic and clinical outcomes, relative to the natural progression of symptoms in the absence of additional intervention. This control arm was designed to be half the size of each active treatment group (n=35), resulting in a total sample size of 173 and preserving a 2:2:1 randomization ratio. This total sample size (n=173) is consistent with a G*Power estimate for a 3 (group)×2 (time) mixed design, assuming a small effect (Cohen *d*=0.30), 80% power, and a Bonferroni-adjusted alpha of .0125 for 4 pairwise comparisons (ie, self-reported self-transcendence; 2 psychophysiological indices of self-transcendence, including frontal midline theta activity and DMN activity, and acute pain). Beyond these primary group-level effects, the planned sample size also supports Aims 2 and 3. Specifically, a G*Power analysis (2-tailed, *α*=.0167, corrected for multiple comparisons; power=0.80) indicated that 112 participants are sufficient to detect a moderate association (*r*=0.30) among phenomenological and psychophysiological indices of self-transcendence, well below the planned sample of n=173. Finally, this sample size is adequate for the planned mediation analyses; the parallel multiple-mediator model for acute pain includes 19 estimated parameters, yielding approximately 9.1 observations per parameter with n=173, consistent with the commonly cited 5‐10 observations per parameter convention.

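### The fixed block size of 6 cannot carry the stated 2:2:1 allocation; the ratio and arm sizes agree with each other, so the block size is the figure that does not fit

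*Protocol article*

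**What the plan says.** The Overview calls the study a "single-blind, randomized, 3-arm, parallel-group, clinical trial (2:2:1 allocation ratio" of the three arms MB, MB+DP and waitlist control. The Participants section repeats the ratio and builds on it: "This control arm was designed to be half the size of each active treatment group (n=35), resulting in a total sample size of 173", which is described as "preserving a 2:2:1 randomization ratio". The two active arms come from the earlier two-arm calculation, in which "a total sample of 138 participants would provide sufficient power".

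The mechanism is in Assignment of Interventions and Blinding. Randomization is stratified by opioid use (yes or no), and for both strata the rule reads: "participants are allocated using permuted block randomization with a fixed block size of 6 to maintain allocation concealment and prevent prediction of assignment". The article does not give the composition of a block, and nothing in it reconciles a block of 6 with a ratio whose parts add to 5.

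**The concern.** In permuted-block randomization every block holds the arms in the target ratio, so the block length must be a multiple of the sum of the ratio's parts. For 2:2:1 that sum is 5, and 6 is not a multiple of it. The randomization rule as printed therefore cannot produce the design as printed.

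This matters for two reasons. First, the arm sizes are part of the sample-size argument. The Participants section says the two-arm calculation was meant to support the comparison of MB with MB+DP, and the Discussion presents that comparison as the core of the dismantling design. A list built on some other split of 6 would change how many participants inform it. Second, the Results section says recruitment began on 28 October 2024 and is expected to be completed by May 2027. The sequence is withheld from the principal investigator and assessment staff until the end of the study. If the list itself is wrong, the people running the trial are not placed to notice while it could still be corrected.

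A smaller issue sits in the same sentence: it credits a single fixed block length with preventing prediction of assignment, which a fixed length does not do by itself.

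**Working it through.** **Inputs.** Ratio 2:2:1 (Overview; Participants). Waitlist n=35, total N=173, two-arm total 138, analyzable sample 110 with 25% inflation (Participants). Block size 6, fixed, within two opioid-use strata (Assignment of Interventions and Blinding).

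**Step 1: reproduce the plan's arm sizes.**
- 110 × 1.25 = 137.5, rounded up to 138.
- 138 / 2 = 69 per active arm. This figure is derived; the article does not print it.
- 69 / 2 = 34.5, rounded up to 35 for the waitlist.
- 69 + 69 + 35 = 173, the stated total.
- From the ratio directly: 173 × 2/5 = 69.2, 173 × 2/5 = 69.2, 173 × 1/5 = 34.6.

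The ratio, the 35 and the 173 are therefore consistent.

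**Step 2: test the block.** At 2:2:1 a block of 6 would need 6 × 2/5 = 2.4, 2.4 and 6 × 1/5 = 1.2 participants. In whole numbers (a, b, c), 2:2:1 requires a = b = 2c, so the block length is 2c + 2c + c = 5c. Setting 5c = 6 has no integer solution. Lengths that work are 5 (2/2/1), 10 (4/4/2), 15 (6/6/3) and so on.

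**Step 3: what blocks of 6 would give at N=173** (MB / MB+DP / waitlist).

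| Block composition | Ratio | Expected arms |
|---|---|---|
| 2/2/2 | 1:1:1 | 57.7 / 57.7 / 57.7 |
| 3/2/1 throughout | 3:2:1 | 86.5 / 57.7 / 28.8 |
| 3/2/1 alternating with 2/3/1 | 5:5:2 | 72.1 / 72.1 / 28.8 |

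**Step 4: illustrate the effect on MB+DP versus MB.** Two-sample t test, two-sided, n per arm, noncentrality d × √(n/2), 2n − 2 degrees of freedom. Assumptions: d=0.6 (the smallest effect the article reports from its preliminary data), alpha .0125 (the article's Bonferroni level), all 173 analyzed.

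| n per arm | Assumed list | Power |
|---|---|---|
| 69 | 2:2:1 | 0.838 |
| 58 | 2/2/2 | 0.755 |
| 72 | 3/2/1 alternating with 2/3/1 | 0.856 |

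The direction depends on which split is assumed. For the comparisons with waitlist, the 2/2/2 list goes the other way: the standard error factor √(1/n₁ + 1/n₂) is 0.208 at 69 and 35, and 0.186 at 58 and 58.

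**The case against.** **The list may be right and the article wrong.** A misprinted block size is as compatible with the documents as a faulty list, and a reader might infer that participants have been misallocated since October 2024. The documents do not support that inference: neither the list nor the block composition is shown. What stands is that the printed rule and the printed ratio cannot both describe the list.

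**Blocks of 6 could average 2:2:1.** One block of 2/2/2, two of 3/2/1 and two of 2/3/1 make 12/12/6 over 30 participants. This is arithmetically possible, but no such scheme is described. If one is in use, the article omits its defining feature and still needs correcting.

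**The ratio and arm sizes might equally be at fault.** They are not equally doubtful. They appear in two sections and reproduce one another; the block size stands alone.

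**The power loss is not established.** This is correct. A reader might infer a definite fall from 0.838 to 0.755, but that holds only for an assumed 2/2/2 list. The alternating split gives slightly more power than 2:2:1. The illustration also ignores attrition, uses a two-sample t test where the plan specifies linear mixed models, and uses d=0.6 although the planning effect is d=0.30. At d=0.30 and alpha .0125 the same formula gives only 0.225 at 69 per arm and 0.183 at 58.

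**Predictability is limited in practice.** A reader might infer that one assignment in six is known in advance. That requires someone to know the block composition, the stratum and every earlier allocation in it, including waitlist assignments. The article does not show that anyone who enrolls participants has this. The list is held by uninvolved personnel, and the interventionist learns active allocations only just before the first appointment. What stands is narrower: a fixed block length is not in itself a means of preventing prediction.

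**Conclusion.** The contradiction is certain and needs no assumption beyond the ordinary meaning of a permuted block: a block of 6 cannot hold 2:2:1. The ratio, the waitlist size of 35 and the total of 173 agree, so the block size is the figure to question first. Because recruitment is under way, this must be settled now.

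The consequence for the trial is unknown until the list is inspected. It ranges from a one-number correction to arm sizes that differ from the design, for instance about 58/58/58 instead of 69/69/35. The power figures are conditional illustrations and are not an estimate of what this trial has lost. The wording on prediction is a secondary fault.

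**What to change.** Ask the independent holder of the randomization sequence to compare the list in use with the stated ratio in each opioid-use stratum, without disclosing allocations to the principal investigator or assessment staff.

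- **If the list delivers 2:2:1:** correct the block size in Assignment of Interventions and Blinding. The cost is one sentence.
- **If it does not and 2:2:1 is to be kept:** generate the remaining allocations in each stratum in blocks that are multiples of 5, preferably varying and undisclosed, such as 5 and 10. Include allocation period in the models, because the ratio will have changed part-way. The cost is a new list for participants not yet randomized, an amendment and one extra model term.
- **If it does not and the actual ratio is to be kept:** state that ratio, whether 1:1:1, 5:5:2 or another, and restate the arm sizes and power. The cost is a text amendment and a recalculation.

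In each case, drop the claim that the fixed block length prevents prediction, or vary the block lengths. None of these routes in itself requires additional participants, unless the restated power in the last case is judged too low.

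### A constant block of 6 cannot deliver the stated 2:2:1 allocation, and the protocol describes no varying scheme that would

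*Protocol article*

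**What the plan says.** The Overview of the Methods describes a "single-blind, randomized, 3-arm, parallel-group, clinical trial (2:2:1 allocation ratio". The Participants section builds the arm sizes. For the original comparison of the two mindfulness groups, "a total sample of 138 participants would provide sufficient power", and "This target reflected a required analyzable sample of 110, inflated by 25% to account for expected attrition". The waitlist was then added: "This control arm was designed to be half the size of each active treatment group (n=35"). On the overall numbers, the section describes this addition as "resulting in a total sample size of 173 and preserving a 2:2:1 randomization ratio". The size of each mindfulness arm is not printed, but it follows as 69.

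The section Assignment of Interventions and Blinding gives the mechanism. "Randomization is stratified by opioid use (yes or no"), and within each stratum "participants are allocated using permuted block randomization with a fixed block size of 6". It does not give the composition of a block and does not mention compositions that vary from block to block. The Results section dates the start of recruitment to October 28, 2024, with completion expected by May 2027.

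**The concern.** The ratio and the block size are both stated in plain sentences, and they do not fit together under ordinary permuted-block randomization. This is a conflict between two stated design rules, so it does not depend on detail that an article would leave to a fuller document.

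The composition of the blocks determines how many participants each arm receives, and so the precision of every between-arm contrast. The Discussion makes MB+DP versus MB the core of the dismantling design. Participants moved from the mindfulness arms to the waitlist weaken that comparison and strengthen the comparisons with the waitlist.

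The timing also matters. Recruitment is under way, and the sequence is withheld from the principal investigator and assessment staff until the study ends, so the people who could notice a wrong ratio are not meant to see it. Allocations already made cannot be undone. Changing the composition part-way would make the allocation probabilities depend on calendar time.

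**Working it through.** **1. The plan's own arm sizes (Participants section).**
- 110 × 1.25 = 137.5, rounded up to 138 for the two mindfulness arms.
- 138 / 2 = 69 per mindfulness arm.
- 69 / 2 = 34.5, rounded up to 35 on the waitlist.
- 138 + 35 = 173. The stated total is reproduced.
- Check from the ratio: 173 × (2/5, 2/5, 1/5) = 69.2 / 69.2 / 34.6.

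**2. Can a block of 6 hold 2:2:1?** The ratio sums to 5, and 6 / 5 = 1.2. A block of 6 would need 2.4 / 2.4 / 1.2 participants. Enumerating all whole-number splits of 6 with equal mindfulness arms and a waitlist half as large finds none. The same search finds 2/2/1 for a block of 5, 4/4/2 for 10 and 6/6/3 for 15.

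**3. Could varying compositions do it?** Two blocks of 3:2:1, two of 2:3:1 and one of 2:2:2 total:
- MB: 3+3+2+2+2 = 12
- MB+DP: 2+2+3+3+2 = 12
- Waitlist: 1+1+1+1+2 = 6

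This is 12:12:6 over 30 participants, or exactly 2:2:1. It is feasible, but the protocol does not describe it.

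**4. Arm sizes if the block is 2:2:2 (assumption).** 173 / 3 = 57.7, so about 58 per arm. Each mindfulness arm loses about 69 − 58 = 11, and the waitlist gains about 58 − 35 = 23. A simulation of stratified blocks, with an assumed 30% of opioid users because the protocol gives no share, put each arm between 56 and 60. Blocks of 5 gave means of 69.2 / 69.2 / 34.6.

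**5. What that would do to the contrasts.** The method is a two-sided two-sample t-test on a single measurement (noncentral t), with all randomized participants analyzed. The noncentrality is d × √(n1·n2/(n1+n2)). Alpha .0125 is the Bonferroni level given in the Participants section. The detectable d at 80% power is:

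| Contrast | Alpha | At 69/69/35 | At 58/58/58 |
|---|---|---|---|
| MB+DP vs MB | .0125 | 0.575 | 0.629 |
| MB+DP vs MB | .05 | 0.480 | 0.525 |
| Either mindfulness arm vs waitlist | .0125 | 0.704 | 0.629 |
| Either mindfulness arm vs waitlist | .05 | 0.587 | 0.525 |

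For MB+DP versus MB, power at the d detectable with 69 per arm falls from 80% to 71.1% (alpha .0125) or 72.7% (alpha .05). For either mindfulness arm versus waitlist, power at the d detectable with 69/35 rises from 80% to about 89% (alpha .0125) or 88% (alpha .05).

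At alpha .0125, the same test of MB+DP versus MB has these powers at the protocol's two effect sizes:
- d = 0.60, the smallest preliminary effect: 84% with 69 per arm and 75% with 58.
- d = 0.30, the planning effect: 22% with 69 per arm and 18% with 58.

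**The case against.** A reader might infer that the two rules can never both hold, that one is already being broken, and that the trial is running at 58/58/58. The text does not support any of these. It fixes the block size but not the composition, and step 3 shows a varying scheme that reaches 2:2:1 exactly. No sentence states 2:2:2, 3:2:1 or any other composition. The mismatch may be only a wording error: the original sizing concerned two mindfulness arms, for which blocks of 6 work as 3:3, and the waitlist was added later, although before enrollment. The ratio appears twice and the block size once. If the actual list is 2:2:1, there is no loss of power at all.

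A reader might also take the fall from 80% to about 71% as a loss in the trial's stated power. It is not. The protocol plans on d = 0.30 in a mixed design with repeated measurements and expects attrition, while the t-test above ignores all three. Quoting only that fall would also be one-sided, because both contrasts with the waitlist gain from equal arms. Concealed 1:1:1 randomization would be unbiased; it would redistribute precision between contrasts.

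All of this stands as a limit on the size of the problem. It does not remove the mismatch: as written, the procedure gives no way to reach the stated ratio, and the block composition in use remains unknown to the reader.

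**Conclusion.** The point holds as an internal contradiction. Ordinary permuted blocks of 6 with a constant composition cannot produce 2:2:1, and the protocol describes no varying scheme that would. That conclusion needs only the stated ratio and block size.

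The effect on arm sizes is conditional. Under an assumed 2:2:2 block, the arms would be about 58/58/58 in place of 69/69/35. By the t-test, at 80% power and alpha .0125, the detectable d for MB+DP versus MB would worsen by about 0.05, and for each mindfulness arm versus waitlist it would improve by about 0.07. These figures compare two sets of arm sizes under one simple test and do not estimate the trial's actual power. Whether the error lies in the sequence or only in the text cannot be settled from the article.

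**What to change.** The independent holder of the sequence should check which block composition has been used in each opioid stratum and report only what is needed to correct the text, without showing the sequence to the principal investigator or assessors.

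- **If the list is truly 2:2:1:** correct the block size in Assignment of Interventions and Blinding to the one used (a multiple of 5), or describe the varying scheme. Nothing else changes.
- **If it is not, there are two options.** One is to keep the ratio in use, correct the ratio in the Overview and Participants sections, and restate the arm sizes and power. This keeps allocation probabilities constant over time. The other is to generate the remaining allocations in blocks that are multiples of 5, report when the change was made and the arm sizes expected, and include allocation period as a factor in the treatment model.

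The cost is one check by the sequence holder and a few corrected sentences. At most it adds a recalculated power statement, or a regenerated list for participants not yet randomized and one model term. No participants are added.

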### Aims

To isolate the specific effect of DP to mindfulness-based pain relief, the Pointing Beyond project will randomize 173 adults with CMP into one of three groups: (1) 4 weekly 30-minute sessions of traditional mindful breathing (MB) instruction, (2) 4 weekly 30-minute sessions of MB combined with DP (MB+ DP) instruction, or (3) a waitlist control group (WLC). The specific aims are:

#### Aim 1

Evaluate between-group differences in changes in self-transcendence from Session 1 to Session 4 across the MB, MB+DP, and WLC groups, using a validated self-report instrument (state version of the Nondual Awareness Dimensional Assessment [NADA-S]; primary outcome) and 2 psychophysiological indices (secondary outcomes), including frontal midline theta activity (via electroencephalography [EEG]) [28,29] and a functional near-infrared spectroscopy (fNIRS) [31] derived proxy default mode network (DMN) activity.

#### Aim 2

Examine the associations among phenomenological and psychophysiological indices of self-transcendence by testing within- and between-session correlations between self-reported self-transcendent state (NADA-S), frontal midline theta activity (EEG), and fNIRS-derived proxy DMN activity across intervention sessions and study groups.

#### Aim 3

Determine whether increases in self-transcendence mediate treatment-related improvements in pain outcomes by testing indirect effects of group assignment (MB, MB+DP, and WLC) on (1) acute pain intensity at the end of Session 4 (secondary outcome) [32] and (2) pain-related outcomes (eg, functional interference) through 3-month follow-up (tertiary outcomes) [33-38], via changes in (1) self-reported self-transcendence (NADA-S), (2) frontal midline theta activity (EEG), and (3) fNIRS-derived DMN activity measured during Session 4, controlling for presession pain and baseline levels of the mediators.

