### Plans to Promote Participant Retention and Complete Follow-Up

To promote participant retention and ensure complete follow-up, the study will implement a structured, participant-centered engagement strategy grounded in best practices for behavioral trial management. All follow-up assessments (at 1-week, 1-month, and 3-month posttreatment) will be conducted remotely via secure, web-based surveys to enhance flexibility and reduce burden. A dedicated RA will serve as each participant’s primary point of contact, maintaining regular communication and providing reminders and technical support based on participant preference (eg, phone, text, or email). Participants will receive modest compensation at baseline, each follow-up, and upon treatment completion, consistent with ethical standards for noncoercive remuneration.

Adherence will be further supported by weekly audio-guided mindfulness recordings and at-home practice diaries. Flexible scheduling will be offered for in-person EEG and fNIRS assessments to accommodate work and caregiving responsibilities. Missed sessions or assessments will be followed up within 48 hours, with up to 3 recontact attempts using alternate methods. Participants may re-engage at the next appropriate activity without penalty and may request a personalized summary of their self-report data poststudy. This approach aims to promote retention and data completeness while minimizing participant burden.

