## Discussion

CMP continues to pose a significant public health burden, in part due to its capacity to become enmeshed with the sense of self. The present randomized controlled clinical trial is designed to move beyond symptom reduction alone by examining whether altering the self-referential structure of pain perception, via DP instruction, can produce meaningful and durable analgesic effects. DP may offer relief by shifting how individuals relate to pain, reducing identification with painful sensations and loosening the pain-laden self-concept that can sustain the pain they endure. The Pointing Beyond project is designed to make 4 key contributions to the field of mindfulness-based pain relief.

The first contribution concerns measurement. By combining momentary self-report with concurrent psychophysiological indices, frontal midline theta activity via EEG and DMN dynamics via fNIRS, this trial moves beyond the retrospective and aggregate outcome data that have characterized most prior work on self-transcendence in mindfulness research. Real-time triangulation of subjective experience and neural activity allows for a more precise characterization of when and how self-transcendent states arise during practice and whether their phenomenological and neurobiological signatures are coherently coupled. This multimodal approach is essential because self-report measures of transcendence are inherently subjective and susceptible to demand characteristics; convergence with independent psychophysiological indices would substantially strengthen causal inference about the mechanism.

Second, a central contribution is the dismantling design itself. Comparing MB alone against MB+DP against a waitlist control isolates the specific contribution of direct pointing instruction to both self-transcendence and analgesia. Prior trials incorporating DP, including RCTs of the MORE program and brief perioperative MBIs, confounded DP with other intervention components, leaving its independent effect unexamined. If MB+DP produces meaningfully greater self-transcendence and pain relief than MB alone, this would provide the first direct evidence that DP adds analgesic value beyond standard mindfulness instruction. This finding would have immediate implications for how brief MBIs are designed and delivered in clinical settings.

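### The claimed assessor blinding can hold only for the remote clinical surveys; the primary outcome, EEG, fNIRS and acute pain are collected in lab sessions with staff who know or can infer the arm

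*Protocol article*

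**What the plan says.** The Overview labels the trial: "This will be a single-blind, randomized, 3-arm, parallel-group, clinical trial". That sentence does not name the blinded party, so the reader must turn to Assignment of Interventions and Blinding. That section gives two safeguards. The allocation sequence is kept from assessment staff and the principal investigator until the study ends. Then: "Outcome assessor blinding will further be ensured through the use of online, asynchronous self-report surveys, preventing any direct interaction between study personnel and participants". The same section says that allocation in the active arms "will only be revealed to the interventionist immediately before" the first treatment appointment, so the therapist is unblinded by design.

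Study Settings describes how the outcomes are collected. Self-transcendence and acute pain are rated in the lab sessions on a tablet running Qualtrics. Of the sessions with psychophysiological recording (1 and 4) it says: "During these sessions, the participant, study therapist, and trained research assistant (RA) will be present". Only the broader clinical questionnaires, at baseline and at the three follow-ups, are completed remotely.

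Aims identifies the lead endpoint: "state version of the Nondual Awareness Dimensional Assessment [NADA-S]; primary outcome".

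**The concern.** The blinding sentence describes a data collection route that the main endpoints do not use. Someone reading the single-blind label together with the assessor-blinding statement would conclude that the primary result is protected from staff influence. As the rest of the article describes it, that protection exists only for the tertiary surveys.

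This matters more here than for a hard endpoint. NADA-S is a three-item subjective rating, and the Discussion itself accepts that "self-report measures of transcendence are inherently subjective and susceptible to demand characteristics". One of its three items measures bliss, and the direct pointing instruction, given in one arm only, directs attention to qualities of awareness that include bliss. In that arm the post-session rating follows an instruction that overlaps with the scale's content. Arm-aware staff close to that rating are what assessor blinding is normally meant to guard against.

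**Working it through.** No formula applies. The check sets each outcome's place, timing and personnel against the blinding sentence.

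| Outcome | When and where (Study Settings, Measures) | Staff present | Remote, asynchronous, no staff contact? |
|---|---|---|---|
| NADA-S | Tablet, before and after lab Sessions 1 and 4 | Therapist and research assistant | No |
| Frontal midline theta (EEG) | Resting baseline and practice period, Sessions 1 and 4 | Same | No |
| DMN proxy (fNIRS) | Same recording periods | Same | No |
| Acute pain | Tablet, before and after Sessions 1 and 4 | Same | No |
| BPI, physical function, PCS, PHQ-2, GAD-2, sleep | Remote Qualtrics survey at T0 to T3 | None in person | Yes, subject to the retention contact below |

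1. **Coverage.** The first four rows are the outcomes that the Participants section names for its Bonferroni threshold: .05 / 4 = .0125. The safeguard covers 0 of these 4. The article calls the EEG and fNIRS measures secondary under Aim 1 and primary in Measures; the count is the same either way. The last row holds the outcomes that Aim 3 and Measures class as tertiary.

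2. **Does the other safeguard fill the gap?** The word *further* in the blinding sentence points back to withholding the sequence. That conceals upcoming assignments. It does not mask a research assistant who is present while breathing practice alone, or breathing practice followed by direct pointing, is delivered, or while a waitlist participant has a control period with no instruction. The therapist is told the arm.

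3. **Does the claim hold in full for the remote surveys?** Not as worded. The retention section makes a research assistant each participant's "primary point of contact, maintaining regular communication and providing reminders and technical support". Reminders are not outcome rating, so this is a secondary tension. It still does not fit a statement that any direct interaction is prevented.

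4. **Could the sentence be read as limited to follow-up?** It contains no such limit. The in-session ratings also run in Qualtrics, so a reader could easily take them to be included.

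**The case against.** The strongest reply is that the endpoints are self-rated. Participants enter their own answers, staff score nothing, and nothing says that anyone watches or reads the tablet. That stands. A reader might infer that NADA-S is rated in front of the therapist. The article says only that the therapist and research assistant are present in these sessions and that the measures are given during them. Nor does it spell out who attends the waitlist visits.

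A reader might also infer that unmasked staff reject EEG or fNIRS channels. The Statistical Analysis section does not support this. Bad EEG channels are identified by a named pipeline and fNIRS motion correction is algorithmic, and who processes the files is detail that an article may leave to a fuller document.

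A third tempting step is to put a size on the bias. The article gives neither a standard deviation for NADA-S nor any estimate of a courtesy shift. The therapist attends both Session 1 and Session 4, so a constant shift would cancel in the Session 1 to Session 4 change. Much of any general wish to please would also be shared by the two active arms, which have the same session structure and length.

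Finally, the article is partly candid already. It concedes that the waitlist does not control for expectancy or facilitator contact, and it looks to agreement with the psychophysiological measures to offset demand effects. Both points stand. Neither makes the blinding sentence true for the primary outcome: the first describes the comparator, and the second concerns interpretation rather than masking.

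**Conclusion.** The concern holds as a contradiction within the article and should be corrected. The assessor-blinding statement can be true only of the remote T0 to T3 surveys, and even there it needs reconciling with the retention contact. It does not cover NADA-S, the EEG and fNIRS measures or acute pain, which is 0 of the 4 outcomes behind the .0125 threshold, in a planned sample of 173.

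This rests on two readings: that Study Settings means what it says about who is present in Sessions 1 and 4, and that a research assistant present during the instruction or control period can tell which arm it belongs to. It does not depend on staff seeing the ratings. The finding is that a stated protection is absent; bias has not been shown, and its size cannot be derived from the article.

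**What to change.** - In Assignment of Interventions and Blinding, limit the sentence to the remote surveys, and remove or reconcile the phrase about preventing interaction with the research assistant contact in the retention section.
- State who is blinded under the single-blind label, and that Session 1 and 4 outcomes are collected with staff aware of the arm.
- For remaining participants (recruitment is expected to run to May 2027), have the NADA-S and pain ratings completed out of view of the therapist and research assistant, with an on-screen statement that the therapist will not see the answers.
- Optionally, code the EEG and fNIRS files without arm labels before processing. This is a precaution, not the repair of a demonstrated error.

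The cost is a wording change, a short procedural step at two visits and a less favourable blinding statement. The step will not remove participants' own knowledge of training versus waitlist, which is inherent in the design. Because it starts part-way through recruitment, record the date so that ratings before and after it can be told apart.
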